**Methods:**

Both trials are cluster-randomized trials among children registered in Bandim Health Project’s rural health and demographic surveillance system throughout Guinea-Bissau. RECAMP-MV is conducted among children aged 9–59 months and RECAMP-OPV is conducted among children aged 0–8 months. We randomized 222 geographical clusters to intervention or control clusters. In intervention clusters, children are offered MV or OPV (according to age at enrolment) and a health check-up. In control clusters, children are offered only a health check-up. Enrolments began in November 2016 (RECAMP-MV) and March 2017 (RECAMP-OPV). We plan 18,000 enrolments for RECAMP-MV with an average follow-up period of 18 months and 10,000 enrolments for RECAMP-OPV with an average follow-up period of 10 months. Data collection is ongoing. The primary outcome in both trials is non-accidental death or non-accidental first non-fatal hospitalization with overnight stay (composite outcome). Secondary outcomes are: non-accidental death, repeated non-fatal hospitalizations with overnight stay, cause-specific primary outcome, outpatient visit, and illness. We obtained ethical approval from Guinea-Bissau and consultative approval from Denmark.

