### Intervention

RECAMP-MV: We offer one dose of a WHO pre-qualified monovalent live attenuated measles vaccine (Edmonston-Zagreb strain from Serum Institute of India) to children aged 9–59 months in intervention clusters.

RECAMP-OPV: We offer one dose of a WHO prequalified standard bivalent OPV to children aged 0–8 months in intervention clusters. To mimic the way most OPV campaigns are implemented, we initiated the RECAMP-OPV trial with two visits one month apart where logistically feasible. At the second visit, a second dose of OPV is offered to children in intervention clusters, while children in both control and intervention clusters are health examined and weighed.

The cold chain for both vaccines is documented. We provide the MV and OPV campaign vaccinations independently from Guinea-Bissau’s routine child vaccination program [26] (Fig. 1).

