After consent, the enrolling nurse performs a health check-up of one child at a time (assessing illness, issues with prior vaccination, and measuring axillary temperature, mid-upper-arm-circumference, and weight). If the enrolling nurse experiences that a child is overtly ill, the child’s mother/guardian is given health advice, and if necessary offered health facility transport, irrespective of cluster assignment. Overtly ill children are offered enrolment at a subsequent visit, if recovered.

If a child is assessed healthy in intervention clusters, the child aged 9–59 months is administered a 0.5 ml reconstituted MV from a 10-dose vial by deep subcutaneous injection into the left subscapular region (leftover doses are discarded six hours after reconstitution), and the child aged 0–8 months is administered two oral drops of OPV from a multi-dose vial (leftover doses are discarded after 28 days). If a child is assessed healthy in control clusters, the child is not administered MV or OPV.

All enrolled children are followed through regular household visits by field assistants who collect information on death and hospitalization, among other. The visits are conducted every two months to children < 12 months of age in Oio, Biombo and Cacheu for logistical reasons, and every six months to older children, and in the remaining regions. If a field assistant registers the death of a child, a specially trained field assistant conducts a verbal autopsy at a subsequent visit [28]. An extra follow-up visit is conducted among a subgroup of enrolled children one-two months after enrolment; the mothers/guardians of these children are visited by field assistants to collect information on outpatient visit and maternally reported illness in the elapsed time span. This visit is also utilized to provide a second OPV dose to children aged 0–8 months in intervention clusters. Figure 2 shows the flow from eligibility to follow-up in RECAMP-MV and RECAMP-OPV.

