### Outcomes

The primary outcome for each trial is defined as a composite outcome to ensure sufficient power. It consists of:
non-accidental mortality ornon-accidental morbidity (first non-fatal hospitalization with overnight stay)

The secondary outcomes assess other health measures. They consist of:
non-accidental mortalitynon-accidental repeated morbidity (at least one non-fatal hospitalization with overnight stay)cause-specific primary outcome (malaria, diarrhea, and respiratory infections [29])proportion of non-accidental outpatient visits and non-accidental maternally reported illnesses in a sub-group 1–2 months after enrolment in the elapsed time spanFurthermore in RECAMP-OPV: weight at the extra follow-up visit 1–2 months after enrolment

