#### Primary analysis of the primary outcome

The main conclusion in RECAMP-MV and RECAMP-OPV will be based on a per-protocol analysis. The primary outcome will be analyzed in a Cox proportional hazards model, adjusted by region, pre-trial vaccination coverage, and sex, with age as the underlying timescale. We will use cluster-robust standard errors to account for intra-cluster correlation. Children will enter the analysis on the day of enrolment, and their follow-up will be censored at:
RECAMP-MV: death due to accident, migration or eligibility for a national MV campaign, whichever comes first.RECAMP-OPV: death due to accident, migration, eligibility for any national vaccination campaign, or a maximum of 12 months of follow-up, whichever comes first.

In both trials, hospital admissions due to accidents are ignored but the follow-up time is censored while the child is admitted.

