#### Secondary outcomes

In per-protocol analyses, we will assess the secondary outcomes: non-accidental mortality, non-accidental repeated morbidity, and cause-specific primary outcome. These secondary outcomes will be analyzed in Cox proportional hazards models as described for the primary outcome. Furthermore, we will analyse outpatient visits and maternally reported illnesses occurring 1–2 months after enrolment in per-protocol analyses using log-binomial regression models adjusted for region, pre-trial vaccination coverage, and sex. In RECAMP-OPV, we will furthermore analyze weight and MUAC 1–2 months after enrolment using multiple regression models adjusted for region, pre-trial vaccination coverage, and sex.

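### RECAMP-OPV: the weight and MUAC regressions at 1–2 months leave out age and the enrolment measurement, so a valid secondary comparison is less precise than the collected data allow

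*Protocol article*

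**What the plan says.** The Secondary outcomes part of the statistical analyses states, for RECAMP-OPV, that "we will furthermore analyze weight and MUAC 1–2 months after enrolment using multiple regression models adjusted for region, pre-trial vaccination coverage, and sex". These are the only covariates named. The Outcomes section lists the endpoint as "weight at the extra follow-up visit 1–2 months after enrolment", with no mention of a change score or an age-standardised score, and it does not list MUAC.

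Other sections show what is available:

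- **Age range.** The abstract says that "RECAMP-OPV is conducted among children aged 0–8 months". Age decides which of the two trials a child enters, so it is known for every child.
- **Enrolment measurements.** Under Enrolment and follow-up procedures, the nurse's check-up includes "measuring axillary temperature, mid-upper-arm-circumference, and weight". It comes before any vaccine is given, so these are true baseline values.
- **Follow-up measurement.** The same section says that "An extra follow-up visit is conducted among a subgroup of enrolled children one-two months after enrolment", and gives no size for the subgroup. The Intervention section says of the second visit that "children in both control and intervention clusters are health examined and weighed".
- **Age in other models.** The primary Cox model is fitted "with age as the underlying timescale", and three of the secondary outcomes follow that model.

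**The concern.** Weight rises quickly over the first months of life, so in a group enrolled anywhere from 0 to 8 months a large part of the spread in follow-up weight reflects age and starting size. The Cox models deal with age through their timescale. A linear regression has no such device, so with only region, coverage and sex as covariates, age drops out of the model.

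Two things follow. First, the residual variance contains variation that the trial has already measured and could remove, so the confidence interval is wider than it need be. The visit reaches only a subgroup, so precision may be limited to begin with. Second, if the enrolled children of the two arms differ in age or size, that difference goes straight into the weight comparison. The Discussion says that there is no allocation concealment and that guardians in intervention clusters might be more motivated to enrol. The analysis is per-protocol among enrolled children, so a difference of this kind need not be chance alone.

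**Working it through.** **The only related figure in the article.** No SD, correlation, ICC, subgroup size or power is stated for weight or MUAC. The nearest stated figure is 80% power for the RECAMP-OPV composite outcome. Inputs: 111 clusters per arm ("We randomized 222 geographical clusters to intervention or control clusters"), rates 0.055 and 0.041 per person-year, 40 person-years per cluster, coefficient of variation 0.25, alpha 0.05 taken as two-sided. The Hayes–Moulton formula gives

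(z_α/2 + z_β)² = (111 − 1) × (0.055 − 0.041)² / [(0.055 + 0.041)/40 + 0.25² × (0.055² + 0.041²)] = 110 × 0.000196 / 0.002694 = 8.00

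so z_β = 2.83 − 1.96 = 0.87 and power is 80.8% (79.2% with an exact 25% reduction). The stated 80% reproduces. It does not involve the weight model, so nothing below changes it.

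**Assumptions for weight.** Correlation r between the enrolment and follow-up measurement: 0.7 to 0.9. ICC: 0.01 to 0.05. Children measured per cluster (m): 10 to 45. The upper end is 10,000/222 = 45, which would mean that every enrolled child had the visit.

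**Formula.** With R² = r² within clusters and R²_b between clusters, the variance of the treatment contrast after adjustment, relative to before, is

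[ICC(1 − R²_b) + (1 − ICC)(1 − R²)/m] / [ICC + (1 − ICC)/m]

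The SE factor is its square root. The number of clusters cancels.

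**Case A: covariates explain both parts equally (R²_b = R²).** The ratio reduces to 1 − r².

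**Case B: no between-cluster variation explained (R²_b = 0), ICC 0.05, m = 45.** The denominator is 0.05 + 0.95/45 = 0.0711. For r = 0.9 the numerator is 0.05 + 0.95 × 0.19/45 = 0.0540, so the ratio is 0.76.

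**Case C: as B, but ICC 0.01 and m = 10.** The denominator is 0.01 + 0.99/10 = 0.109. For r = 0.9 the numerator is 0.01 + 0.99 × 0.19/10 = 0.0288, so the ratio is 0.26.

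| r | A: variance ratio (SE factor) | B: variance ratio (SE factor) | C: variance ratio (SE factor) |
|---|---|---|---|
| 0.7 | 0.51 (0.71) | 0.85 (0.92) | 0.56 (0.75) |
| 0.8 | 0.36 (0.60) | 0.81 (0.90) | 0.42 (0.65) |
| 0.9 | 0.19 (0.44) | 0.76 (0.87) | 0.26 (0.51) |

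**Is the assumed r reasonable for weight?** An illustrative simulation used an assumed infant growth curve, ages spread evenly over 0–8 completed months, follow-up 1–2 months later and no clustering. Relative to a model with sex alone, residual variance fell to 0.38–0.68 with age added and to 0.08–0.27 with enrolment weight added. With enrolment weight, age and visit interval it fell to 0.03–0.24. The range of r above is therefore not extravagant for weight, but the growth curve is an assumption and not a figure from the article. No such check was made for MUAC.

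**The case against.** The strongest case against has four parts.

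- **The loss can be overstated.** A reader might infer that the planned model throws away most of the available precision, or that adjustment is worth two to five times as many children. Those figures come from 1/(1 − r²), which is 1.96 at r = 0.7 and 5.26 at r = 0.9, and they hold only in Case A. Even there, losing more than half requires r above 0.71, and the article gives no r. In Case B the planned model already keeps 76–85% of the attainable precision. Moreover, adding children within a fixed set of clusters does not reduce between-cluster variance, so a sample-size equivalence misleads. This objection stands.
- **No bias is shown.** Chance imbalance in age is already part of the unadjusted standard error and is not a second harm. A reader might infer that the planned estimate is invalid, but the documents do not support that. What remains is conditional: if enrolment differs by arm in age or size, which the Discussion leaves possible but does not report, adjustment removes the measured part of that difference.
- **MUAC is weaker ground.** It is not in the outcome list, and the second-visit description mentions weighing only. The size estimates should be read as applying to weight.
- **The RECAMP-OPV data analysis plan (Additional file 2) is not shown.** It may define the outcome form or handle the visit interval, so the absence of days since enrolment is not a fault in itself. For age and the enrolment value the argument has less force, because the article names its covariates. If the plan adds others, the two texts need reconciling.

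**Conclusion.** The point holds as a matter of efficiency. The article names a covariate list for weight and MUAC that omits two strong and available predictors, age at enrolment and the enrolment value of the same measure. The analysis remains valid. For weight, under the assumed r of 0.7–0.9, the standard error would be multiplied by 0.71–0.44 in the favourable case. The factor is only about 0.9 if the covariates explain no between-cluster variation, the ICC is around 0.05 and all enrolled children have the visit. The variance falls in every scenario examined, but by how much cannot be settled from the documents, and for MUAC it is less certain still. Protection against measured age or size imbalance is a further benefit of unknown size. The consequence is confined to a secondary, subgroup analysis in RECAMP-OPV. The change is worth making, but the trial's main conclusion does not depend on it.

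**What to change.** In the RECAMP-OPV analysis plan, and in any text that repeats the covariate list, model follow-up weight on the enrolment weight, age at enrolment (flexibly, for example with a spline), sex, region and pre-trial coverage. State cluster-robust standard errors for this model. Do the same for MUAC with enrolment MUAC, and bring the outcome list into line on whether MUAC is an outcome. Days since enrolment may be added as an option, since the visit falls anywhere from one to two months after enrolment.

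The change needs no new data, only plan wording. The article already provides for discussing plan amendments with the data safety and monitoring board. It should be fixed before these outcomes are examined by arm. One small cost needs a sentence: the article imputes no missing values, so children without an enrolment measurement would drop out of the adjusted model. Their number by arm should be reported, with the currently planned model kept as a sensitivity analysis.

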#### Effect modifier analyses of primary outcome

In per-protocol analyses we will assess potential effect modifiers of the primary outcome (Tables 3 and 4).

**Table 3 Tab3:** RECAMP-MV - potential effect modifiers

*Effect modifiers*	*Rationale*
Prior MV status	Prior MV administration may lead to a larger reduction in non-accidental mortality/non-accidental morbidity than no prior MV administration [13, 14, 39, 40]
Sex	Girls may experience a larger reduction in non-accidental mortality/non-accidental morbidity than boys [40–43]
Season	Enrolment in the dry season may lead to a larger reduction in non-accidental mortality/non-accidental morbidity than enrolment in the rainy season [29, 44]
Campaigns with other health interventions	Vitamin A may amplify a beneficial non-specific effect [45]. Inactivated meningitis A and inactivated polio vaccination [42], and oral polio vaccination [17, 46], may neutralize/invert a between cluster difference. Participation status will be assigned on an ecological level, assuming that children eligible for campaigns with other health interventions receive these interventions on the campaign dates.

**Table 4 Tab4:** RECAMP-OPV - potential effect modifiers

*Effect modifiers*	*Rationale*
Sex	Previous studies have demonstrated that the effect of OPV is stronger in boys than girls [4, 15, 47].
One vs two doses (2nd dose 1 month after enrolment)	Observational studies indicate that additional doses of OPV offer additional benefits [15].
Age at first dose of OPV	A prior study has indicated that the effect of subsequent vaccines may vary with the age at which the gut was primed [16].
Season of enrolment	Some interventions (eg MV and Vitamin A) have stronger effects when given in the dry season [29, 48]. We will investigate whether the effect of OPV varies for children enrolled in the dry season (December–May) versus children enrolled in the rainy season (June–November)
Vitamin A supplements	Vitamin A supplementation may amplify the NSEs of vaccines [49, 50]. We will examine whether the effect of OPV vary before and after being eligible for vitamin A supplementation after enrolment
Prior OPV campaign	Repeated doses of OPV offer additional benefits [15]. If OPV campaigns take place during the study, we will assess whether the effect is similar in children having been exposed/not exposed to prior OPV campaigns.

#### Sensitivity analyses of primary outcome

We will assess the robustness of the primary analysis of the primary outcome for each campaign under different scenarios:
two intention-to-treat analyses: 1) in a classic intention-to-treat analysis children will be included if present in the cluster from the day they were first potentially eligible to enter but did not because they e.g. did not receive the assigned treatment, were excluded due to illness, did not have a mother/guardian to escort them, or had a mother/guardian who refused participation, 2) in an extended intention-to-treat analysis children will be included if living in the cluster from the day they were first potentially eligible to enter (including children from the classic intention-to-treat analysis and children who were absent/travelling) as either campaign may affect other children’s health in the community by reducing the general infectious pressure.Furthermore, we will assess if different censoring criteria affect the robustness of the results

## Ethics and dissemination

Prior to initiating the trials, we obtained ethical approval from Guinea-Bissau’s national ethics committee (Comité Nacional de Ética na Saúde: CNES/2016/020) and consultative approval from Denmark’s national ethics committee (Den Nationale Videnskabsetiske Komité: 1606756). Then we met with all regional health directorates to inform them about the trials’ aim, routines, initiation date, and to request their collaboration. This paper includes amendments resulting from our discussions with the data safety and monitoring board and the sample size enlargements. For these amendments, we obtained ethical approval from Guinea-Bissau’s national ethics committee (Comité Nacional de Ética na Saúde: CNES/2018/028) and consultative approval from Denmark’s national ethics committee (Den Nationale Videnskabsetiske Komité: 1606756). The trials are registered at www.clinicaltrialsgov.com (identifier NCT03460002). Data is being stored according to a general agreement between the BHP, and the Ministry of Health in Guinea-Bissau, and Statens Serum Institut in Denmark. At the BHP’s main office in Guinea-Bissau all questionnaires are physically stored, and databases with enrolment and follow-up information are separately stored at an encrypted server.

We will disseminate the results regardless of positive or negative findings. We intend to publish the results in internationally peer-reviewed journals. We will provide the results to WHO, and Guinea-Bissau’s Primary Health Program, Institute of Public Health and regional health directorates; the Institute of Public Health will receive a copy of the results. Any significant deviations from this paper will be documented in the reported results.

## Discussion

This paper presents the methodology of two concurrent cluster randomized controlled trials named RECAMP-MV and RECAMP-OPV. We will assess the real-life effect of an MV campaign among children aged 9–59 months (RECAMP-MV) and the real-life effect of an OPV campaign among children aged 0–8 months (RECAMP-OPV) on non-accidental mortality or non-accidental morbidity (composite outcome) in rural Guinea-Bissau**,** where measles infection is limited and no polio circulates. Major strengths lie within the cluster randomisation design which allows us to assess each campaign’s effect on the general infectious pressure, which would not be possible with individual randomisation. Furthermore, the BHP’s rural HDSS ensures a reliable and thoroughly tested data collection and data management infrastructure minimizing the risk of loss to follow-up. In the following, we consider a major limitation, circumstantial challenges, and future perspectives.

The major limitation is insufficient blinding. Only blinding health system personnel can make the campaigns appear to have an effect that does not solely depend on the campaigns. However, blinding the research group, field teams and mothers/guardians would require placebo use. Administering another vaccine may trigger NSEs, which could obscure the assessment of the campaigns’ NSEs. Administering saline would be causing many children pain without benefit. However, as death and hospitalization are not subjective, and as their assessment is based on standardized interviews, we expect the risk of differential outcome reporting to be minimized. Though, we do have some speculations about the potential impact of not blinding the mothers/guardians: 1) mothers/guardians in intervention clusters may consider their children as being extra healthy because they have seen their children receive the campaign vaccines. This could make the mothers/guardians less prone to seek help from the health system if their children get ill. Thus, among children whose mothers/guardians state that their children have been ill after enrolment we will assess the proportion of children whose mothers/guardians also state an outpatient visit by cluster assignment. 2) mothers/guardians in intervention clusters could come to know that their children belong to an intervention cluster prior to enrolment because there is no allocation concealment. This could make the mothers/guardians in intervention clusters more motivated to let their children enrol than mothers/guardians in control clusters. Thus, we will assess if there is a difference in the proportion of children whose mothers/guardians choose not to participate for different reasons, by cluster assignment.

We could face some circumstantial challenges. For RECAMP-MV: 1) Guinea-Bissau’s low risk profile makes a measles epidemic seem unlikely. It is nevertheless possible. Our regular contact to the AEFI and disease surveillance responsible in the health regions also ensures registration of suspected measles infection cases. However, declared measles infection cases are likely to be misclassifications of other childhood infections as BHP has experienced in previous studies from Guinea-Bissau. Therefore, only reported measles infection cases when regional health directorates confirm circulating measles will be classified as measles. In such instances, field assistants are instructed to pose questions about symptoms, timing, and source of infection based on BHP’s rural HDSS questionnaires used in previous studies. 2) if Guinea-Bissau’s Ministry of Health does not announce a national MV campaign during the trial, we will conduct a visit to all children enrolled in control clusters to offer them MV after both trials have ended. For RECAMP-OPV: national OPV campaigns implemented during the trial will shorten the follow-up period, which could reduce the power.

In both trials, it may influence enrolment efficiency that we exclude children from other ongoing BHP trials in rural Guinea-Bissau. However, we expect to have included a sufficient number of clusters to avoid under-powering due to this potential challenge.

If RECAMP-MV and/or RECAMP-OPV demonstrate beneficial NSEs of the expected respective magnitudes in the absence of measles and/or polio infections, it will clearly challenge two understandings. Firstly, MV and/or OPV only prevent measles and/or polio infections. Secondly, once measles and/or polio infections are eradicated MV and/or OPV campaigns can be phased out, saving resources and without any negative implications for child health and survival; phasing out the smallpox vaccine seems to have had an impact on survival in both high [51] and low-income countries [52, 53]. Furthermore, demonstrated beneficial NSEs in RECAMP-OPV will highlight the need to identify alternative ways to keep stimulating the immune system after the discontinuation of OPV in routine vaccination program services.

